### Data analysis

All data will be doubly entered into a password-protected computer 1 week after data collection. The statistical analysis will be performed by SPSS 22.0 for Windows by a single statistician. The scores will be analysed by the intent-to-treat analysis. The last observation carried forward method will be used for missing data. Comparisons of continuous variables between the acupuncture and sham groups will be assessed using Student’s t-test or analysis of covariance (ANCOVA) with baseline measures as covariates. Comparisons of categorical data between groups will be tested by the χ^2^ test or the Mann–Whitney U-test. Changes in the scores from baseline within treatment groups will be assessed by the paired t-test or the Wilcoxon signed ranks test. Data from the patient diary will be assessed to analyse covariate balances in the two groups. If we find an imbalance, we will use the propensity score method [31] or the conditional inference method [32] to remove the confounding effect. All statistical tests will be two-sided at a 5% significance level.

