**Fig. 1 Fig1:**
[figure not shown]
Flow diagram of the study protocol. Assessment measures will be performed as follows: (1) Pain: VAS (visual analogue scale) and WOMAC (Western Ontario & McMasters University Osteoarthritis Index); (2) Functional movement: TUG (Timed up & Go Test) and 8-step SCT (Stair Climb Test); (3) Quality of life: Short Form-36 (SF-36); (4) Credibility test (end of weeks 2 & 4); (5) Test of blinding success (end of week 4); (6) Patient diary (weekly)

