### Exclusion criteria

Subjects will be excluded if they meet any of the following criteria: (i) are unable to walk; (ii) have a serious infection of the knee; (iii) have suspected tears in any ligaments or menisci or acute inflammation of the synovial capsule; (iv) have a history of trauma, ligament damage, fracture, or surgery on the knee(s) within 6 months, causing pain or functional problems (history of knee replacement will be excluded); (v) have a history of local tumour/malignancy at the knee; (vi) have physical or laboratory findings indicating infection, presence of autoimmune disease or inflammatory arthritis; (vii) have knee pain caused by radiculopathy/herniation of an intervertebral disc; (viii) have end-stage diseases or other suspected severe conditions such as deep vein thrombosis of the lower limb, oedema related to cancer or cancer treatment, severe blood coagulation disorders, uncontrolled systemic arterial hypertension and severe diabetes; (ix) have a history of prolotherapy, hyaluronic acid injections or corticosteroids injections within 3 months; (x) have received acupuncture, electro-acupuncture, Tui-na therapy, massage, or physiotherapy 8 weeks prior to enrolment in the trial; (xi) have severe pain in other regions; (xii) have severe mental disorder(s); (xiii) are oversensitive to needles; and (xiv) are insensitive to pain due to advanced diabetes, neuropathy or use of strong painkillers.

Eligible subjects will receive baseline assessments and will be randomly allocated to the sinew acupuncture group (*n* = 43) or the sham acupuncture group (*n* = 43) in a ratio of 1:1 by block randomization. The random digits and letters will be generated by SPSS, covered by aluminium foil, and sealed into opaque envelopes.

Subjects will be advised not to receive other acupuncture treatments, Tui-na, massage or physiotherapy. Subjects are not restricted from the use of painkillers (including herbs) or external ointments if they suffer intolerable pain. The use of rescue medications, the daily level of morning stiffness and exercise time will be recorded in patient diaries.

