### Outcome measures

The VAS at week 4 will be the primary outcome. The WOMAC, TUG, 8-step SCT, and SF-36 scores will be the secondary outcomes. The assessment schedule is shown in Table 1. Independent assessors who are not involved in acupuncture treatments will perform the VAS assessments (asking subjects to indicate the pain intensity at the most painful points during walking and ascending/descending a step and overall). Acupuncturists will complete a “Physical Examination and Treatment Form” including details of the medical history, diagnosis and treatment procedures. The acupuncturists will communicate with the subjects using neutral language. The administration of analgesics, external ointments and herbal medicines and the time of daily exercises will be collected weekly from patient diaries during the intervention period and at each visit during the follow-up period.

**Table 1 Tab1:** The schedule of enrollment, interventions, and assessments

Items	Enrollment	Allocation (baseline)	Interventions (± 2 days)										Follow-up	
Time points (week)	-2	0	1			2			3		4		6	10
Treatment sessions (n)	–	–	1	2	3	4	5	6	7	8	9	10	–	–
Eligibility screen	✓													
Informed consent	✓													
VAS		✓	✓	✓	✓	✓	✓	✓	✓	✓	✓	✓	✓	✓
WOMAC		✓			✓			✓		✓		✓	✓	✓
SF-36		✓										✓		✓
TUG		✓						✓				✓	✓	✓
8-step SCT		✓						✓				✓	✓	✓
PE & Tx		✓	✓	✓	✓	✓	✓	✓	✓	✓	✓	✓	✓	✓
Patient Diary					✓			✓		✓		✓	✓	✓
Credibility Test								✓				✓		
Test of Blinding Success												✓		
Adverse events			✓	✓	✓	✓	✓	✓	✓	✓	✓	✓	✓	✓

PE & Tx, Physical Examination and Treatment Form; SCT, stair climb test; SF-36, 36-item short form; TUG, timed up & go test; VAS, visual analog scale; WOMAC, Western Ontario and McMasters University Osteoarthritis Index

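### An imbalance in diary data collected after randomisation triggers adjustment as if it were confounding, which can bias the intention-to-treat effect in either direction

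*Protocol article*

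**What the plan says.** All references are to the protocol article.

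- **Trigger (Data analysis).** "Data from the patient diary will be assessed to analyse covariate balances in the two groups".
- **Consequence (Data analysis).** "If we find an imbalance, we will use the propensity score method [31] or the conditional inference method [32] to remove the confounding effect". The same paragraph promises an intention-to-treat analysis and compares arms by t-test or by ANCOVA with baseline measures as covariates.
- **Diary content (last paragraph under Exclusion criteria).** "The use of rescue medications, the daily level of morning stiffness and exercise time will be recorded in patient diaries".
- **Diary timing (Outcome measures).** Analgesics, ointments, herbal medicines and exercise time "will be collected weekly from patient diaries during the intervention period", and at each follow-up visit. In Table 1 the "Patient Diary" row is first ticked at session 3 in week 1, then at sessions 6, 8 and 10 and at weeks 6 and 10. The enrolment and baseline cells are empty.
- **Order of events (under Exclusion criteria).** "Eligible subjects will receive baseline assessments and will be randomly allocated to the sinew acupuncture group". Allocation follows the baseline assessments, so no scheduled diary collection precedes it.

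**The concern.** A confounder of a treatment comparison has to influence, or share a cause with, who receives the treatment. Here allocation is random and comes before every scheduled diary entry, so a diary variable cannot have affected allocation. A difference between arms in such a variable is either chance or a consequence of treatment.

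All three diary items can plausibly respond to treatment. Stiffness is a symptom of the disease and a WOMAC domain. Painkiller use is permitted for intolerable pain, so it depends on pain after allocation. Exercise time may change as the knee improves or worsens. If treatment moves any of them, the rule conditions on part of what treatment did, and the adjusted contrast no longer estimates the total effect that an intention-to-treat analysis targets.

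The rule is also data-driven. Whether to adjust, and by which of two methods, is decided after looking at post-randomisation data. The estimate of the primary outcome, VAS at week 4, could shift as a result.

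**Working it through.** **1. The plan's own figure.** From Sample size estimation: change with sinew acupuncture 17.9 mm, assumed sham change 10.74 mm, SD 10.7 mm, two-sided alpha 0.05, power 0.80.

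- Difference: 17.9 − 10.74 = 7.16 mm. Standardised: 7.16 / 10.7 = 0.669 (the article gives 0.673).
- Two-sample t-test: 36.04 per group with 0.669, which rounds up to 37; 35.6 with 0.673. The stated 37 per group is reproduced.
- Power at 37 per group with 0.669: about 81%.

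**2. Timing.** Random allocation follows baseline assessment; the first diary collection is at session 3. Every scheduled diary variable is post-randomisation.

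**3. Illustration for a stiffness-like variable.** The documents give no diary effects, so the inputs here are assumptions. Let treatment improve the diary variable by s SD, and let r be its within-arm correlation with week-4 VAS. In a linear-normal model:

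adjusted effect = 0.669 − r × s

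| s | r | removed (r × s) | share of 0.669 | adjusted effect |
|---|---|---|---|---|
| 0.3 | 0.3 | 0.09 | 13% | 0.58 |
| 0.5 | 0.5 | 0.25 | 37% | 0.42 |
| 0.669 | 0.6 | 0.40 | 60% | 0.27 |

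**4. Power in the middle row, regression adjustment, 37 per group.**

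- Residual SD: √(1 − 0.5²) = 0.866.
- Variance inflation from the correlation between arm and diary variable: 1 + 0.5²/4 = 1.0625.
- Standard error: 0.866 × √(2/37 × 1.0625) = 0.208.
- Non-centrality: 0.419 / 0.208 = 2.02, giving power of about 51%. Simulation agrees (0.51).
- With propensity-score weighting in place of regression, simulated power is about 40%.

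**5. Direction can reverse.** Suppose treatment reduces rescue medication by 0.5 SD and each SD of use lowers VAS by 3 mm (both assumed). The part carried by rescue use is (−0.5) × (−3) = +1.5 mm, so the adjusted effect is −7.16 − 1.5 = −8.66 mm. Simulation with the propensity score gave about −8.7 mm. Here adjustment enlarges the estimate.

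**6. Null check.** When treatment does not move the diary variable, the simulated adjusted estimate stays at about −7.1 mm. The bias comes from treatment affecting the variable.

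**The case against.** Several points on the other side are fair.

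- **Adjustment is conditional and its role is not spelled out.** A reader might infer that the adjusted result replaces the primary comparison. The text does not say so, nor which outcomes the step covers. Equally, it does not confine the step to a sensitivity analysis. This limits how strongly the point can be put but does not remove it.
- **Direction.** A reader might infer that adjustment always removes part of a real effect. That fits stiffness, but step 5 of the working shows that it need not hold for rescue medication. The documents support bias in either direction and no more.
- **When the rule fires.** A reader might infer that it fires exactly when treatment has worked. With 43 per arm, imbalance also arises by chance, and treatment can work without a visible diary difference.
- **Which variables.** Data analysis names no adjustment variables, and the list of diary items in Outcome measures omits stiffness. Stiffness comes in through the description of the diary under Exclusion criteria. That it would be adjusted for is a reasonable inference, not a stated rule.
- **Implementation.** The two cited method papers are not at hand. However they are implemented, conditioning on the same post-randomisation variables raises the same problem.
- **Unequal co-medication is a legitimate interest.** This stands, but it is a different question from the intention-to-treat effect and should be labelled as such.

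An unseen analysis plan does not excuse the rule: the article states the trigger, the methods and the rationale, so this is not a detail left for later.

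**Conclusion.** The rule is wrong as written. The diary data that trigger the adjustment are collected only after randomisation, so an imbalance in them is not confounding, and adjusting for it can bias the total effect in either direction. That conclusion rests on the schedule and the text alone and is firm.

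The size is not firm. The loss of 13% to 60%, and the fall in power from about 81% to about 51% (regression) or about 40% (weighting), depend wholly on assumed diary shifts and correlations. The upper end supposes that treatment moves the diary variable as much as it moves VAS. The inflation to about −8.7 mm is equally assumed. These figures show that the effect on the primary result could be material; they do not predict it.

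**What to change.** 1. Remove the diary-triggered propensity-score or conditional-inference step from the primary efficacy analysis, and stop describing a diary imbalance as confounding.
2. Use ANCOVA with prespecified covariates measured before randomisation (baseline VAS) for the primary comparison. Data analysis already names ANCOVA with baseline measures.
3. Report rescue-medication use, morning stiffness and exercise time by arm as outcomes.
4. Keep any analysis that accounts for rescue use only as a labelled supplementary analysis, with its estimand stated in advance.

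The cost is wording in the protocol and analysis plan; no new data and no change in sample size are needed. Issuing the diary at the existing enrolment visit (week −2), so that pre-randomisation entries could serve as covariates, is optional and not needed for the fix.

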## Discussion

KOA is one of the most common diseases among the elderly. This study will evaluate the efficacy of sinew acupuncture for pain reduction, functional movement improvement, and QOL improvement in KOA patients. In our clinic, there are 8–10 new KOA patients each month. We estimate that recruitment will be completed in 10 months.

The study is conducted in collaboration with the School of Chinese Medicine, Department of Diagnostic Radiology and Department of Orthopaedics & Traumatology, Li Ka Shing Faculty of Medicine, HKU. The eligibility of KOA subjects will be assessed by clinical physicians. The intervention will be performed by experienced acupuncturists. The subjects and assessors will be blinded to subjects’ allocations. The acupuncturist will not be involved in assessments or data entry. Data will be analysed by an independent statistician.

In acupuncture RCTs, it is critical to choose an appropriate control population. Vickers AJ et al. found that acupuncture was superior to both sham and no acupuncture controls for osteoarthritis pain with effect sizes of 0.16 and 0.57, respectively [18]. The small effect size in trials with sham acupuncture controls may be due to the following reasons: (1) the meta-analysis excluded outlying studies showing a very large effect size [18] and (2) according to Macpherson H, Vickers AJ, et al. in the same research group, acupuncture has a smaller effect size in trials with needle-insertion sham controls than in trials with needle non-insertion sham or non-sham controls [15]. Our previous study was consistent with their findings that acupuncture trials with needle non-insertion controls lead to more positive conclusions than those with needle-insertion sham controls [16]. In the present study, we will use needle non-insertion as the control, which may produce a smaller, nonspecific effect compared to needle-insertion sham controls. However, it should be noted that the effect size estimated from our pilot study [29] is larger than that of the previous study by Vickers AJ et al. [18]. If the power estimates prove to be high, the trail can be used to determine a more accurate effect size for future power calculations.

This trial will expand our knowledge of whether sinew acupuncture will reduce pain intensity, improve the symptoms and movements of KOA patients, and improve QOL. If this study is successful, the effectiveness of sinew acupuncture may be studied using a pragmatic trial design.

## Abbreviations

KOA: Knee osteoarthritis
QOL: Quality of life
SCT: Stair climb test
SF-36: 36-Item short form survey
TUG: Timed up & go test
VAS: Visual analogue scale
WOMAC: Western Ontario and McMasters University Osteoarthritis Index
